**Summary of revision history**

| Ref No   | Date | Person   | Version | Reason |
|-----------------|-------------|-----------------|----------------|---------------|
| NLnavigation1.0 | 13-FEB-2013 | [name] | 1.0            |               |
| NLnavigation1.0 | 25-MAR-2013 | [name] | 2.0            | revision      |
| NLnavigation1.0 | 19-AUG-2013 | [name] | 3.0            | revision      |
| NLnavigation1.0 | 16-DEC-2013 | [name] | 4.0            | revision      |
| NLnavigation1.0 | 25-OCT-2014 | [name]    | 5.0            | extension     |
| NLnavigation1.0 | 22-SEP-2015 | [name]    | 6.0            | extension     |
| NLnavigation1.0 | 18-JAN-2016 | [name]    | 7.0            | Extension     |
| NLnavigation1.0 | xxx         | [name]      | 8.0            | Extension     |

**LIST OF ABBREVIATIONS AND RELEVANT DEFINITIONS**

|                |                                                                                                                                                                                                             |
|----------------|-------------------------------------------------------------------------------------------------------------------------------------------------------------------------------------------------------------|
| ABR     | ABR form, General Assessment and Registration form, is the application form that is required for submission to the accredited Ethics Committee (In Dutch, ABR = Algemene Beoordeling en Registratie) |
| AE      | Adverse Event                                                                                                                                                                                        |
| AR      | Adverse Reaction                                                                                                                                                                                     |
| CA      | Competent Authority                                                                                                                                                                                  |
| CCMO    | Central Committee on Research Involving Human Subjects; in Dutch: Centrale Commissie Mensgebonden Onderzoek                                                                                          |
| CRLM    | Colorectal liver metastases                                                                                                                                                                          |
| CV      | Curriculum Vitae                                                                                                                                                                                     |
| DSMB    | Data Safety Monitoring Board                                                                                                                                                                         |
| EU      | European Union                                                                                                                                                                                       |
| EudraCT | European drug regulatory affairs Clinical Trials                                                                                                                                                     |
| GCP     | Good Clinical Practice                                                                                                                                                                               |
| IB      | Investigator's Brochure                                                                                                                                                                              |
| IC      | Informed Consent                                                                                                                                                                                     |
| METC    | Medical Research Ethics Committee (MREC); in Dutch: medisch ethische toetsing commissie (METC)                                                                                                       |
| (S)AE   | (Serious) Adverse Event                                                                                                                                                                              |
| SPC     | Summary of Product Characteristics (in Dutch: officiële productinformatie IB1-tekst)                                                                                                                 |
| SUSAR   | Suspected Unexpected Serious Adverse Reaction                                                                                                                                                        |
| Wbp     | Personal Data Protection Act (in Dutch: Wet bescherming persoonsgegevens)                                                                                                                            |
| WMO     | Medical Research Involving Human Subjects Act (in Dutch: Wet Medisch-wetenschappelijk Onderzoek met Mensen)                                                                                          |

---

**SUMMARY****Rationale:**

Image-guided navigation surgery allows for full utilization of pre-operative imaging during surgery, and has the potential of reducing both irradical resections and morbidity. This is the first feasibility and safety registration study towards clinical implementation.

**Objectives:**

*Primary:* Feasibility and safety of an in-house developed electromagnetic navigation system during abdominal surgery.

*Secondary:* Evaluation of the accuracy of the system. During the procedure, possible improvements of the navigation hardware and software will be recorded and the handling during surgery will be evaluated. Extra time needed to use the navigation system during surgery will be recorded.

**Study design:**

An observational registration study.

**Study population:**

Patients undergoing scheduled for abdominal surgery by laparotomy. A total of 95 patients will be included in this study.

**Intervention:**

Extra contrast enhanced CT-scan of the pelvis and abdomen one day preoperatively. One extra intra-operative XperCT scan during surgery (no contrast). Identification of iliac vessels and ureters during surgery using an image-guided navigation probe. If a rigid tumour, or pathologic lymph nodes along the large vessels are present, the navigation system will be used to localize them.

**Main study parameters/endpoints:**

Feasibility, safety and handling of an electromagnetic navigation system during abdominal surgery.

**Nature and extent of the burden and risks associated with participation, benefit and group relatedness:**

Participation in the study will not involve additional visits to the hospital for the included patients. Patients will be informed for the study during the pre-operative outpatient clinic appointment. Informed consent will be obtained before or at admission to the hospital at least one day before operation.

One day before surgery, when patients are already admitted to the hospital, a contrast-enhanced CT-scan of the abdomen is performed. During the scan three removable electromagnetic reference-marker patches are placed on the skin at superficial bony

---

structures of the pelvis, such as the anterior superior iliac spine. The CT scan will be used to create a three-dimensional anatomical reconstruction of the organs at risk within the pelvis. Before surgery, the reference-markers will be positioned at the same locations. An intra-operative XPerCT scan will be used to assess the exact marker positions in the OR setup. The reference-markers will be used during surgery to correlate the CT scan to the actual patient position. During surgery, the iliac vessels and ureters will be identified using the guidance of a blunt tip probe of the navigation system. Total time of the proposed measurements, including intra-operative scan, will take no longer than 20 minutes. It is highly unlikely that the iliac vessels and ureters will be damaged during this procedure, since the navigation procedure is aimed at navigating towards the structures, without disrupting the patient's anatomy. When the tumour is rigid, e.g. sacral invasion, or when pathological lymph nodes are present outside the standard total mesorectal excision region, the navigation system will be used to localize these structures. The total burden for the patient will be one additional contrast enhanced CT scan, one XPerCT scan, and an extension of the total surgery procedure with no more than 20 minutes.

This is a registration study to evaluate the overall performance, safety and potential benefit of the surgical navigation system during abdominal surgery. The surgeons are aware of the experimental setup, and are therefore responsible for the navigation interpretation and actions. The eventual goal of this project is to judge the potential use of the navigation system for further clinical studies. When the system proves safe and accurate, further studies will be directed to improve tumor free surgical resection margins in abdominal surgery as well as to reduce the morbidity rate by more selective resections sparing more healthy tissue by intra-operative navigation.

## 1. INTRODUCTION AND RATIONALE

### ***Clinical problem:***

Standard treatment of rectal cancer consists of pre-operative (chemo-) radiation followed by surgical resection of the rectum. Resection can be challenging, especially in patients with large tumours, recurrent disease or tumours that have been treated with a long scheme of chemo-radiation. In these patients, anatomical planes are disturbed due to the tumour ingrowth, fibrosis or radiation effects. This can impede tumour free resection margins as well as the identification of surrounding structures (e.g. ureters and hypogastric plexus) and hence could result in damage of these structures. In distal rectal cancer, the number of resections that still contain tumour tissue at the resection edge mounts up to 30%. Better intra-operative guidance could improve these results significantly.

Damage to the ureters during surgery for pelvic tumours leads to reinterventions, long time morbidity and even perioperative mortality. The incidence of ureteric damage varies between 0.5 and 10% in most series and is highly dependent of the type and extend of the surgical intervention. The incidence of damage to the hypogastric plexus approaches 30%. Damage of the hypogastric plexus results in bladder dysfunction (e.g. urine retention, stress or urge incontinence, loss of bladder sensitivity) and sexual disorders (e.g. erection and ejaculation disorders, decreased vaginal lubrication). Bladder dysfunction occurs in 20-30%, and sexual disorders in approximately 30% of patients after rectal surgery. These complications have a significant impact on the patients' quality of life.

### ***Integration of imaging during surgery***

Pelvic tumours are diagnosed and judged on resectability using MRI and CT images. All the pre-operative information gathered from these scans is currently used during surgery by means of the "surgeon's brain", i.e. the surgeon reviews the information preoperatively and translates it into actions during surgery. The pre-operative images become more valuable when they are available during surgery and when the real-time positions of surgical tools can be related to the preoperative images during surgery. Fitted in a 3D environment, this would provide better assessment of resection planes and avoidance of vital structures. Image guided navigation systems can be used to integrate preoperative imaging in the surgical procedure.

### ***Background of intra-operative navigation:***

The continuously improving quality of medical imaging as well as the development of the supporting computer systems have led to the rise of image guided navigation in surgery. Pre- and per-operative acquired images (*e.g.* CT, MRI, ultrasound) are the key imaging modalities in navigation and are used to create three-dimensional road maps used for localization, orientation and guidance during surgery. In order to utilize the road map, a tracking system needs to be used which enables the correlation of the preoperative imaging to the actual position of the patient on the operation table. When implemented, the application of navigation during surgery results in three-dimensional insight and offers a view beyond the surfaces of organs. Furthermore, it can be used to reproduce pre-operative resection planning. This novel technique will be part of the operating room of the future and can lead to safer, tissue sparing and oncological more accurate procedures with an improved clinical outcome.

The application of image guided navigation is under investigation in many surgical fields. It is well established in surgical procedures of rigid structures such as bone and brain. Historically, neurosurgeons are the key players in this field and have already advanced to clinical studies to assess the effect of their navigation techniques. Navigation in neurosurgery originated from frame-based stereotactic procedures and is nowadays generally applied in the treatment of gliomas and brain metastases. In orthopedic surgery navigation is used in pelvic screw fixation, leading to reduced malposition rates, and in musculoskeletal tumor resection. ENT (ear, nose and throat) and maxillofacial surgeons apply navigation techniques in various procedures such as posttraumatic craniofacial reconstruction of the skull and cochlear implantation.

The above mentioned fields of surgery are all based on the rather fixed positions of the bone and soft tissue components. Retroperitoneal organs, *e.g.* kidney, adrenal glands and iliac vessels can also be considered as relatively fixed and are therefore accessible targets for navigation surgery using preoperative images. Adrenalectomies were performed in a pilot setting using a laparoscopic navigation system^10. Video overlay of reconstructed three-dimensional CT-images onto real-time laparoscopic footage was successfully tested in laparoscopic nephrectomies.

A technically more challenging field for surgical navigation is the abdomen. Organ movement, breathing motion and tissue deformation make the maintenance of accurate anatomical representation during the procedure very complex. More importantly, intra-abdominal targets such as colon or rectum tumors often do not have a fixed position. To accomplish real-time surgical navigation in the presence of “moving targets” a novel surgical tracking and navigation system needs to be developed.

---

There are two main technical options for surgical tracking systems. The first is optical tracking, which is based on a set of 2D or 3D camera's which can be used to detect active or passive markers on the patient and on surgical instruments. Secondly, electromagnetic (EM) tracking can be used, which is based on a magnetic field generator and EM-sensitive sensors. The position of a sensor in the magnetic field is associated with generation of a specific current, revealing the sensor position. Optical tracking systems are known for their accuracy, which is sub-millimeter, but they are dependent on a direct line-of-sight between the camera's and the markers in order to provide positional information. Due to the nature of magnetic fields, EM-navigation systems do not depend on a line-of-sight, while the systems have an accuracy of 1-2 mm. A further challenge for EM systems is the influence of ferromagnetic material on the stability of the generated magnetic field.

In our project we aim to develop a navigation system for colorectal cancer surgery which gives us real-time information on the position and orientation of the tumor. Simultaneously, the system will also be used to visualize and localize organs at risk with respect to the tumor. Since the tumor is not visible during the majority of surgical procedures, the use of optical tracking systems is limited. We are developing and implementing a surgical image-guided EM navigation system in which traceable sensors are implanted in or near the tumor to provide the surgeons with real-time information on the tumor location and orientation. Reference sensors, which are placed on the patient surface during acquisition of preoperative scans, are used during surgery to relate the imaging information to the actual patient position during surgery. Organs at risk which are relatively rigid with respect to the reference sensors, such as the iliac vessels and a large part of the ureters, can be located using the reference sensors. This is also valid for pathologic lymph nodes which are located near the large vessels, as well as for tumors which are rigid due to invasion of pelvic structures. The final system with implanted sensors in the tumor will provide accurate information on tumor position and extent for radical resections independent of the mobility of the tumor, and simultaneously, better insight in organs at risk for reduced morbidity.

The aim of this project is to gain first experience with the electromagnetic navigation system and its application during abdominal surgery. This first step encompasses the evaluation of the feasibility and safety of the system. Furthermore, the accuracy of the system to identify anatomical landmarks and structures with a relatively fixed position, such as iliac vessels, ureters, and fixed tumor deposits is assessed.

---

## 2. OBJECTIVES

The aim of this study is to gain experience using the electromagnetic navigation system for accurate identification of anatomical structures during abdominal surgery.

### Primary Objective:

Feasibility and safety of an in-house developed electromagnetic navigation system during abdominal surgery.

### Secondary Objectives:

Evaluation of the accuracy of the system. Evaluation of possible improvements of the navigation hardware and software, especially the handling in preparation towards and during surgery. Extra time needed to use the navigation system during abdominal surgery will be recorded.

### ***Further clinical development and perspectives:***

It is our aim to develop a fully integrated electromagnetic navigation system for colorectal cancer surgery. This system should provide accurate real-time information on the exact location and orientation of the tumour, the vital surrounding structures as well as the surgical instruments during the procedure. To provide real-time feedback of the location of the tumour, we are investigating the possibility of placing sensors in or around the tumour. However, as explained earlier, in the present project sensors patches will only be placed on the body surface of the patient. A secondary goal is to integrate this system in a laparoscopic environment. Image overlay techniques will be used to create a real-time virtual laparoscopic view where tumour, surrounding structures and instruments are superimposed over the regular laparoscopic view in the correct direction and dimensions. This results in a virtual environment where the surgeon is able to look beyond the surfaces of anatomical layers and organs.

---

### 3. STUDY DESIGN

#### General

The study is designed as an observational registration study.

Patients eligible for inclusion into this study are patients admitted to The Netherlands Cancer Institute – Antoni van Leeuwenhoek (NKI-AvL) and are planned to undergo scheduled abdominal surgery by laparotomy.

#### Procedures

- One day before surgery a contrast-enhanced CT-scan of the pelvis and abdomen is performed. During the scan three removable electromagnetic marker-patches are placed on superficial bony structures of the pelvis, such as the anterior superior iliac spine. Locations will be marked precisely with a permanent marker.
- Segmentations and three-dimensional reconstructions are made of the pelvic bone, the iliac vessels and ureters using the CT-scan
- The resulting 3D reconstructions are evaluated by the surgeon who will perform the surgical procedure.
- Before surgery, the marker-patches will be positioned at the scan locations and the navigation system will be calibrated. Patch positioning is checked in the safety procedure described below (5.2).
- The 3D reconstructions will be loaded into the navigation software.
- An intra-operative XPerCT (no contrast fluid used) is acquired to assess the actual patch positions with respect to the 3D model. The XPerCT is used to improve the navigation accuracy.
- A fast and robust safety procedure will be performed before application of the sterile field, to get an estimate of the registration and navigation accuracy. If tolerance limits are exceeded, the navigation procedure during surgery will be cancelled. The exact safety protocol is described in section 5.2.
- During the surgical procedure, the iliac vessels and ureters will be identified by the surgeon using the guidance of a blunt tip probe of the navigation system.
- Total time of the proposed measurements, including intra-operative scan, will take no longer than 20 minutes. Extra time will be recorded in this study.
- If pathologic lymph nodes or a rigid tumour is present in the patient, the location will be reviewed by means of the navigation system. This localization is not expected to increase the total surgery time, and will often even reduce surgery time.

---

## **4. STUDY POPULATION**

### **4.1 Population (base)**

Eligible patients are patients of the Netherlands Cancer Institute (NKI-AvL), who are scheduled for abdominal surgery by laparotomy. In the enrolment process the “patient informatie” will be used and the informed consent must be signed prior to the intervention.

### **4.2 Inclusion criteria**

- Patients who are scheduled for abdominal surgery
- Locally advanced T3 or T4 tumour or local recurrent tumour
- Patients should be suitable for contrast enhanced CT scanning
- A signed informed consent
- Patients  $\geq 18$  years old

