### **4.4 Sample size calculation**

This project is a proof of principle study. The goal is to assess feasibility and safety of the electromagnetic navigation system in a clinical environment during surgery. The system is already extensively tested in a non-clinical setting and has shown to be highly accurate. Pre-clinical tests within the OR have shown that some environmental changes might influence the accuracy of the system. However, assessing all combinations of possible environmental changes is impossible. We have to perform this registration study to have an estimate of the expected environmental influences during surgery.

During the course of the study, we have identified an import application for navigation; i.e. locally advanced T3 or T4 rectal tumour and tumour recurrences in the abdomen and pelvic area. Lately, due to logistic reasons (OR planning), the drop-out of patients who signed informed consent was higher than expected. In order to obtain sufficient accuracy measurements to obtain statistical relevant numbers in this study, 20 more patients should be included. This accounts for 15 successful measurements and 30% chance of failure.

---

Inclusion of maximally 95 patients will be sufficient to evaluate and improve the system during abdominal surgery. No sample size calculation is performed.

---

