## 5. TREATMENT OF SUBJECTS

### 5.1 Study procedure

All included patients are already scheduled for surgery. The programmed surgical procedure will not in any way be influenced by the measurements, other than an extension of total operating time by a maximum of 20 minutes, which is clinically acceptable in surgical procedures which generally take over 3 hours.

Specific study procedure:

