#### In the OR:

- In the OR the patient will be placed on the table according to standard protocol, with the exception that the EM field generator will be placed between the table and the patient (Fig. 1).
- The marker-patches will be positioned at the scan locations and the navigation system will be calibrated.
- The 3D reconstructions will be loaded into the navigation software.
- An intra-operative XPerCT (no contrast fluid used) is acquired to assess the actual patch positions with respect to the 3D model. The XPerCT is used to improve the navigation accuracy.
- Before surgeons start applying the sterile field, an estimate of the registration accuracy between the CT and actual marker positions will be performed. If tolerance limits are exceeded, the navigation procedure during surgery will be cancelled.
- At the moment the laparotomy is advanced to the stage in which the iliac vessels are visible for the surgeon the study measurements are started.
- After the measurements the surgeon will proceed with the standard surgery. If the tumour is rigid, or pathologic lymph nodes are present around the large vessels, the navigation system can be used to localize them.

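### Section 4.2 sets no tumour site and does not require iliac exposure, so a patient eligible as written may be scanned without being able to give the accuracy measure

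*Protocol*

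**What the plan says.** **Who may enter.** Section 4.1 takes patients "scheduled for abdominal surgery by laparotomy". Section 4.2 restates this as "Patients who are scheduled for abdominal surgery" and adds "Locally advanced T3 or T4 tumour or local recurrent tumour". It names no organ or region, and neither 4.2 nor 4.3 mentions exposure of the iliac vessels. Section 4.4 describes the application that emerged during the study as "locally advanced T3 or T4 rectal tumour and tumour recurrences in the abdomen and pelvic area".

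**What is measured, and where.** Under Procedures in Section 3, "three removable electromagnetic marker-patches are placed on superficial bony structures of the pelvis". Section 5.1 fixes the start: "At the moment the laparotomy is advanced to the stage in which the iliac vessels are visible for the surgeon the study measurements are started". The surgeon then points, without seeing the navigation screen, at the aortic bifurcation and at the left and right internal/external iliac bifurcations. Sections 6.1 and 8.1 use these three points as the objective distance measure. The ureters are graded by surgeon's opinion. The main endpoint in 6.1 is framed through the iliac vessels and ureters.

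**What the study may not do.** Section 5.1 states "The programmed surgical procedure will not in any way be influenced by the measurements", apart from added operating time. Section 5.2 limits pointing to regions that are already visible and approachable.

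**What is claimed.** The primary objective in Section 2 is "Feasibility and safety of an in-house developed electromagnetic navigation system during abdominal surgery". Accuracy is a secondary objective.

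**The concern.** The eligibility rule and the measurement rule do not cover the same patients. Eligibility depends on tumour stage or recurrence. Measurement depends on whether one anatomical region is open to view. Nothing in Section 4 links the two.

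Three things are at stake. First, the contrast CT is done the day before surgery, and 5.1 lists the XPerCT before the sterile field is applied. Both scans are therefore spent before anyone sees whether the vessels come into view. Second, a case without exposure says nothing about how the system performs, and the protocol does not say how to count it. Section 6.3 withdraws patients when technical or physical problems prevent measurement. Non-exposure could be read into that rule and vanish from the feasibility result, or it could be booked as a failure of the system. Third, all objective accuracy data come from one region, while the objective is worded for abdominal surgery at large.

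**Working it through.** This is mainly a comparison of sections. One figure in the plan can be checked.

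**The plan's own figure.** Section 4.4 adds 20 patients to obtain 15 successful measurements with a 30% chance of failure.
- 15 × (1 + 0.30) = 19.5, rounded up to 20, which is the stated figure.
- 15 / (1 − 0.30) = 21.4, rounded up to 22, which is the usual inflation for a 30% loss.
- Expected successes from 20 patients: 20 × 0.70 = 14.

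The stated 20 is reproduced by the first formula and lies within two patients of the second. This arithmetic neither supports nor refutes the present point. It shows only that the extension has no slack for a further loss. If a share s of eligible patients had no iliac exposure, and this came on top of the 30%, the expected yield would be 14 × (1 − s). If it were already inside the 30%, the yield would stay at 14. The protocol gives no s and does not say what the 30% covers, so no count of affected patients follows.

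**Setting the sections side by side.**

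| Step | Section | Requirement |
|---|---|---|
| Eligibility | 4.1, 4.2 | Laparotomy; T3/T4 or local recurrence; no site |
| Stated application | 4.4 | Rectal T3/T4; recurrences in abdomen and pelvis |
| Patches | 3, 5.1 | Pelvic bone |
| Start of measuring | 5.1 | Iliac vessels in view |
| Objective points | 5.1, 6.1, 8.1 | Aortic bifurcation, two iliac bifurcations |
| Limits on access | 5.1, 5.2 | Operation unchanged, anatomy not disrupted |

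1. A T3 or T4 tumour outside the rectum meets 4.1 and 4.2 but lies outside the 4.4 description.
2. A recurrence elsewhere in the abdomen meets 4.1, 4.2 and 4.4. Adding the word rectal to the T3/T4 criterion would therefore not close the gap.
3. In either patient, if the planned operation does not reach the iliac vessels, the start condition in 5.1 is not met and the access limits bar the study from creating it. The three points cannot then be recorded.
4. By then both scans have been done and a place has been used.

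Other details suggest that a pelvic field was assumed. Section 4.3 excludes metal implants only in the pelvic area, and the caption of Figure 1 in 5.2 refers to pelvic cancer surgery. The assumption was never written as a criterion.

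**The case against.** The strongest reply is that this is a small wording gap and that much of what might be built on it fails. Most of that reply is right.

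- A reader of 4.2 alone might infer that laparoscopic patients are admitted. They are not. Section 4.1, Section 3 and the Summary all require laparotomy, and 4.1 and 4.2 are read together. What remains is that 4.2 does not repeat the requirement.
- A reader might infer that 4.4 restricts the study to rectal tumours. It does not, because it names recurrences in the abdomen too. Only T3/T4 tumours outside the rectum go beyond it.
- A reader might infer that a known number of patients is lost. No case mix is given, no operation without exposure is reported, and the only cause of drop-out that 4.4 names is OR planning.
- A reader might infer that the abdominal-surgery objective is left untested. Feasibility and safety are primary. Extra time, handling and adverse events can be recorded in any open abdominal operation, and 8.1 cross-references tumour boundaries and suspected nodes with pathology. Section 1 also already describes accuracy as assessed for structures of relatively fixed position.
- A reader might take Section 1 to say that the pelvis is easy and the abdomen hard. It contrasts fixed with moving targets. It counts rectal tumours among the moving ones and kidneys and adrenals among the relatively fixed.

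A practical objection is that a change now comes late. If the 20 added patients are part of the 95, then 95 − 20 = 75 places came before them, and a new criterion would divide the cohort. That is a real cost. It calls for reporting the change openly and does not justify leaving the criterion as it is.

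None of this supplies the missing link between eligibility and exposure.

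**Conclusion.** The point holds as a mismatch between eligibility and measurement, with a limited consequence for the accuracy claim. As written, the protocol can enrol a patient whose planned operation never meets the condition for starting measurement, and it does not say how that patient is counted. The objective accuracy results can support conclusions only about relatively fixed structures near the iliac tract, because no objective point lies above the aortic bifurcation.

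The size is unknown. That such patients exist is an inference from the criteria, and it rests on one assumption: some eligible laparotomies do not expose the iliac vessels. The documents neither confirm nor exclude this. They do not support the stronger conclusions that the number lost can be estimated or that feasibility and safety in abdominal surgery are not examined. The correction is worth making because it is cheap and each affected patient undergoes two additional scans.

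**What to change.** 1. **Section 4.2.** Repeat the laparotomy requirement of 4.1. Reconcile the tumour site with 4.4, so that both sections describe the same population. Add that exposure of the aortic and iliac bifurcations must already be part of the planned operation.
2. **Sections 2 and 8.1.** State that accuracy conclusions apply to the relatively fixed structures described in Section 1, near the iliac tract, and not to abdominal surgery in general. The feasibility and safety objective can keep abdominal surgery as its setting.
3. **Sections 6.3 and 8.1.** Keep every included patient in the feasibility denominator. List non-exposure of the landmark by the planned operation as a separate reason for no measurement, and do not remove such patients as withdrawals. Setting them outside the denominator after the event could flatter feasibility. Listing the reason lets a reader separate it from failure of the system. Apply this to patients already enrolled as well, and report results before and after the change in criteria.

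The cost is a few sentences and slightly fewer eligible patients, including some abdominal recurrences that 4.4 names. Those lost could not have given the landmark measure, although they would have contributed data on handling, time and safety.
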